#### **Funding**

This trial was supported by a grant from the Dutch foundation "Stichting tot Steun VCVGZ" (grant nr: 431), and by additional funding from collaborating mental health centres.

## **SMALL CHANGES MADE TO THE ORIGINAL PROTOCOL dd. 6th June 2021**

- **COVID-19:** Due to COVID-19, the last 50 assessments of the 18-months follow-up measurements were made by phone/videocall.
- **Sample size:** We planned to include 180 participants. Our power calculations showed that 133 was needed in order to take possible drop-out into account. Our final sample included 158 participants, but our drop-out was less than anticipated. Thus although our sample size was smaller, this did not have an effect on the power of the analysis.
- **Participating centers and teams:** We had planned to recruit patients in nine mental health care centers throughout the Netherlands, with each center agreeing on participating with two teams at the time of writing the protocol. However, one team declined to participate, and there were 3 centers that included an extra team. Thus, recruitment took place at nine mental health centers, with a range of 1 to 3 teams per center.
- **Included patients per team:** We expected to reach a mean of N = 10 participants per team with a range of 6 to 14. There were however two teams that only recruited two patients, and there was one team that included 18 patients. Our range of patients per team was hereby larger than expected.

## **BACKGROUND AND RATIONALE**

The number of adults (18 to 65 years) with severe mental illness (SMI) in Dutch mental health care is estimated up to 160.000 (Delespaul et al., 2013). People with SMI not only have to cope with their psychiatric symptoms but also with serious impairments in psychosocial and community functioning. Indeed, the nationwide survey “Panel Psychisch Gezien” in the Netherlands in 2016 (N=1519) revealed that many report problems of loneliness (more than 80%) and not being part of the society (40%). Moreover, only 20% has paid employment (including social employment) (van Hoof et al., 2016). The impoverished social environment is also reflected by the finding that 76% of long-term psychiatric patients name their professional as the most important person in their life (Borge, Martinsen, Ruud, Watne & Friis, 1999). However, people with SMI tend to have the same needs in life as other citizens but they seem to be in a disadvantageous position to realize these (Couwenbergh, et al., 2014). Good collaboration and communication between the patient, family, community resources and professional care would offer a promising starting point for an improved social and community integration for people with SMI.

Moreover, in the current health policy in the Netherlands there is a growing awareness for the importance of involving patients in their own care. That is, an increasing tendency is observed towards a health care system in which people with SMI are stimulated to be in control of their own lives, to use their own strengths and capacities in creating a meaningful daily living and to participate in society according to their own needs and wishes (Van Hoof, Van Erp, Boumans & Muusse, 2014). This evolving movement in Dutch mental health care is also referred to as recovery-supporting mental health care. Importantly, in this context recovery refers to ‘learning to live better in the face of mental illness’ (Davidson, Tondora & Ridgway, 2012) and it comprises multiple dimensions. Next to the often used clinical recovery (remission of clinical symptoms); personal recovery and societal recovery are thought to be determinants in the process towards a meaningful living in which people with psychiatric symptoms can retain grip on one’s life and participate in society (Dröes & Plooy, 2010). Empowerment is developing into one of the key elements in this renewed view on providing good mental health care. It has been argued that recovery can only be successful if one feels capable

to recover or- in other words- feels empowered (De Haan & Oude Bos, 2011). The concept can be defined as processes in which the person rediscovers his identity and self-esteem and “takes his life in his own hands” (Boevink, Kroon, Delespaul & Van Os, 2016). Empowerment is recognized both as an outcome by itself, as well as an intermediate step to long-term health status and disparity outcomes for the individual (Wallerstein, 2006).

A promising way to increase empowerment and social integration is using Resource Groups (RG) (Nordén, Malm & Norlander, 2012a). RG may offer a new structure in Dutch mental health care to implement both improved social and community integration and the recent developments around recovery and empowerment in clinical practice. In the RG method, significant others from both the informal (friends, family, relatives) and the formal (social workers, nurses, case manager, psychiatrist) support system are systematically engaged in the treatment by means of the resource group meetings. The method is built around the basic theme that patients themselves are the directors of the group and choose their own RG members, set the goals for their treatment and have a decisive impact on how the RG meetings are designed (Nordén, Eriksson, Kjellgren & Norlander, 2012b). This change in structure and patterns of mental health care is a crucial factor in the empowerment of the patient. Empowered patients working in effective collaboration with their RG, in turn, are thought to improve their own health outcomes in terms of increased well-being and improved social and community functioning. Moreover, this process could become an important force in controlling health care costs (Nordén et al., 2012a). Additionally, systematically involving the informal support system of patients and paying attention to their role and burden related to the disease of the patient might reduce their stress and improve their psychological well-being. In other words, the patient’s personalized network is also empowered. As a consequence, there will be more stability within the direct environment of a patient and a lower degree of expressed emotions (EE). This way, supportive environments that supplement professional care in a collaborative manner can be realized.

The RG method has its origin in the “Optimal Treatment” model (OT model), integrating biomedical, psychological and social strategies in the management of severe mental illnesses (Falloon & Fadden, 1993). The treatment is focused on home-based assertive case management integrated with pharmacotherapy, with family or individual psychoeducation, and social and problem solving skills training offered when indicated (Petersen, et al., 2005; Falloon, Held, Roncone & Laidlaw, 1998). Within the OT model, the “family unit in the community” appeared to be an important element and evolved into a new concept in the beginning of the 2000’s in Sweden: the ‘Resource Group’ (Jonsson & Malm, 2002). Here, the RG was embedded within the Resource Group Assertive Community Treatment (RACT) program (Nordén, et al., 2012b). The RACT program is a person-centered flexible assertive community treatment approach placing its emphasis on empowerment and rehabilitation of the client, delivered through a novel mechanism: a resource group clinical microsystem for each patient (Malm, Ivarsson & Allebeck 2014). A clinical microsystem is defined as a small group of people (including health professionals, patients and families) who work together in a defined setting on a regular basis to create care (Nelson, Batalden & Godfrey, 2007).

The first RCT study on the effectiveness of RACT showed significant improved social function and consumer satisfaction in favour of RACT, when compared with a well-established best practice community-based program that combined antipsychotic medication, family interventions and social skills training (Malm, et al., 2003). The main clinically important difference between the two treatment programs was that in RACT the treatment team not only consisted of professionals, but also of the patients and their significant others in which the concept of “shared decision making” was

central in order to formalize the participation of the patients and their significant others in contributing to the care.

A meta-analysis including 17 studies and a total of 2263 psychotic patients on the effectiveness of the RACT program for psychotic patients showed impressive effect sizes. That is, the study revealed that participation in the RACT program resulted in improved (social skills) functioning, increased well-being as well as a reduction of symptoms when compared to CAU, with effect sizes of respectively  $d = .82$ ,  $d = 0.88$  and  $d = .72$  (Nordén et al., 2012a). The combined measure for the 17 studies and the three outcome parameters yielded a large effect size ( $d = 0.80$ ). A review summarizing the findings of eight RCT's concluded that the RACT program consisting of involving patients and their significant others by clinical microsystem resource groups yielded positive effects on symptoms, functioning and well-being for patients with psychoses and that the method may be of use for patients within the entire psychiatric spectrum (Malm, Lundin, Rydell, Nordén & Norlander, 2015).

Although the RACT program comprises various new elements, the Resource Group (RG) has been classified as a major key component (Jonsson & Malm, 2002; Nordén et al., 2012b). The crucial focus in the RG model is on involving patient themselves and their significant others in the treatment and the treatment goals and on reinforcement of the client's own self-confidence and ability (empowerment). This way, all available resources in and around the patient are mobilized and integrated in order to shape most effective care. However, no study has been performed on the added value of the RG method. To isolate the RG as the potential declarative mechanism of the promising results of the RACT program, further research is needed. Moreover, knowledge is lacking about the effectiveness for patients within the entire psychiatric spectrum as well as potential obstacles and cost-effectiveness of implementing the RG-method in Dutch Mental Health care. Therefore, the present study will test the effectiveness of the RG method, the implementation, costs and meaning in a randomized controlled trial (RCT) in the Netherlands for patients within the entire psychiatric spectrum.

## **AIMS**

The primary objective of the present study is to investigate the effectiveness of the Resource Groups on patient outcomes compared to care as usual alone for people with severe mental illnesses. It is hypothesized that participation in the RG is associated with increased empowerment, improved well-being and enhanced social and community functioning, when compared to care as usual.

The secondary objective is to investigate whether care as usual with RG is more cost-effective than care as usual alone. The RG method is hypothesized to be more cost-effective on the long term than care as usual.

The third objective is to explore the implementation process of the RG in Dutch mental health care and the deeper meaning for patients; and to assess potential obstacles, bottlenecks and success factors by using a qualitative case-approach.

## **STUDY DESIGN**

### **Setting**

The study will take place within the context of Flexible Assertive Community Treatment (FACT) (Van Veldhuizen, 2007). Investigations of the RG method in other contexts are also desirable in the future,

but this is beyond the aims of the present study. FACT is a community based outpatient treatment and rehabilitation program, intended primarily for individuals with severe mental illness. A multidisciplinary team of professionals (psychiatrist, psychologist, nurses, social worker, etc.) provides integrated care and support for the patient. The care is provided both at the mental health centers and in the own environment of the patient. Participating teams are generic FACT teams at the cooperating mental health centers for people with SMI and early psychosis (both are in this proposal referred to as FACT-teams).

### **Design and Allocation**

The study is a multicenter randomized clinical trial (MRCT), including 180 patients of nine Dutch mental health care centers.

An independent statistician of the Trimbos Institute will generate a computerized allocation list, stratified on mental health care centers and teams. That is, for each team of every mental health care center a separate allocation sequence will be generated by means of allocation blocks assuming a maximum of fourteen participants per team. Two sizes of allocation blocks are used (i.e. 2 and 4), yielding three possible cells (i.e.: 2x4 and 2x2; 1x4 and 5x2; 0x4 and 7x2). These cells in turn, are randomized to keep the allocation unpredictable for the different stakeholders (care-givers and researchers). In order to minimize the risk of imbalance between conditions, the ratio of these possibilities will be stratified on resp. 1:2:2. The allocation sequence will be stored with the independent statistician and is concealed from all researchers, caregivers, and participants. Once allocated, condition is passed on to the central researcher and local staff by email so that the local intake procedure can be continued. Further matching between patient and case manager is allowed and performed by the local staff of the FACT-team. At start of the baseline measurement (0 months), written informed consent is obtained. Further assessments take place 9 (T1) and 18 (T2) months after obtaining informed consent.. Local independent research assistants will carry out all assessments. Assessments comprise self-report questionnaires (administered on PC) and interviews, see Table 1 and Table 2. Given the nature of our study, blinding of participants and treating clinicians is not possible. The local research assistants however are blinded. To optimize similarity in assessments, research assistants use an extensive standardized study protocol and discuss process in regular telephonic and face-to-face meetings with the central researcher.

Moreover, a qualitative case analysis will be performed in order to assess the implementation process, identify specific helpful and non-helpful aspects of the used protocol and to gain insight into the meaning of the RG method for patients, group members and professional caregivers. To this end, 8 to 10 patients and their RG (including case manager) are asked to participate in a qualitative study and will be monitored for a substantial period of time using an embedded multiple case study design (Yin, 2014). The selection of patients is performed by asking whether the patient approves to be approached for the qualitative research at the end of the baseline measurement of the quantitative study. Then, a selection will be made by using the data from the baseline measurement and optional consult of the case-manager. Some variation in the selection will be pursued (in location, new patients or longer in care, size and composition of the resource group, moderate/good therapeutic working relation). The case selection takes place in two steps with an interval of several months. Based on the first interview experiences, new cases will be sought to ultimately get a good picture of the core and variety of the experiences in the resource groups (purposive sampling). Some main topics that will be investigated are: helpful and harmful aspects of the RG, relationships within the RG, privacy aspects within the group and supervision and

training of case managers. The central researcher and an experienced researcher of Trimbos- specialized in qualitative study designs- will perform this part of the study. Participation of this part of the study is voluntarily and independent of participation of the quantitative part. All participants (both patients and their RG-members) will receive a transcript of the interviews and the observations and are asked to verify whether their opinion is expressed correctly (member check).

[figure not shown]

Fig 1. Randomization and assessment procedure

*NB: if the incoming patients are not enough, patients who entered FACT care in the past 12 months will be screened on inclusion criteria and all will be informed about the RG. They will then follow the same procedure (starting with step 2).*

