## **Recruitment**

Patients are recruited in nine mental health care centers throughout the Netherlands that each agreed on participation with two teams (BAVO Europort, GGZ NHN, GGZ inGeest, Lentis, GGZ Centraal, Antes, Breburg, Altrecht and Arkin). All incoming patients at the participating sites are checked for inclusion criteria by the local staff. Patients meeting the criteria are informed about the study and the RG during intake and asked to participate by the local intaker(s). If patients indicate to be interested, they will receive a patient information brochure and a week time to neutrally consider their participation. They will also be referred to the central researcher for any remaining questions, to ensure that they are fully informed about the nature of the study. Hereafter, the local staff of the FACT-team will contact the patient to inquire whether he/she wants to participate in the study. When the patient verbally agrees with participation the randomization is performed. To this end, the local staff sends a notification email to the central researcher with minimal contact information (surname and telephone number). The central researcher will perform the randomization by entering the following information to the generated allocation list: (1) name of the mental health care center; (2) name of the team; and (3) the sequential number of entry of the new participant. The local researcher will contact the patient to make the first appointment for the baseline measurement. Before start of the baseline measurement, participants sign written informed consent of which they will receive a copy.

In case the number of incoming patients is not enough, patients within the caseload of the trained casemanagers who entered FACT care in the past 12 months will be screened on inclusion criteria and all will be informed about the RG. They will follow the same procedure as described above. The aim is to include as much as possible participants per site, expecting to reach a mean of  $N=10$  per site (ranging from 6 to 14). Recruitment will take place between September 2017 and September 2018, with follow up ending on September 2020.

For both inclusion and follow-up assessments, participants are contacted via the personal information they have provided and approved to use for the study. These entail surname and telephone number. They will be contacted through phone after which they can decide on the location to meet the researcher for the assessments.

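### The protocol contradicts itself on who holds and runs the allocation list, its per-team blocks of mostly 2 do not keep allocation unpredictable to recruiting staff, and one cell has 12 slots, not 14

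*Protocol*

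**What the plan says.** Custody. Under Design and Allocation, an independent statistician generates the list, and "The allocation sequence will be stored with the independent statistician and is concealed from all researchers, caregivers, and participants". Once allocated, the condition is emailed to the central researcher and local staff. Under Recruitment, local staff notify the central researcher of a patient who has agreed verbally, and then "The central researcher will perform the randomization by entering the following information to the generated allocation list". The information entered is the centre, the team and the patient's sequential number.

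Block scheme. Each team has its own sequence, "assuming a maximum of fourteen participants per team". Blocks of 2 and 4 are combined into three cells, "2x4 and 2x2; 1x4 and 5x2; 0x4 and 7x2", and "the ratio of these possibilities will be stratified on resp. 1:2:2". The section says the cells are randomised so that care-givers and researchers cannot predict the allocation.

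Who recruits. Under Recruitment, local staff check eligibility, inform eligible patients, and later ask whether the patient wants to take part. Randomisation follows directly on a verbal yes. Treating clinicians are not blinded (Design and Allocation).

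**The concern.** Three statements about one list do not fit what surrounds them.

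- **Custody.** A list hidden from all researchers cannot, without further explanation, be the list on which a researcher performs the randomisation.
- **Predictability.** Varying the block pattern protects a sequence only if past allocations say little about the next one. Here the people who screen and invite patients learn every earlier result in their own team, and most blocks are as short as a block can be.
- **Length.** The first cell does not add up to the stated maximum.

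At stake is selection bias. If staff can foresee the arm, their judgement of eligibility, or how warmly and when they approach the next patient, can depend on it. Adjusting for measured covariates does not reliably remove such bias. Assessor blinding gives little protection either, because it acts after entry and the primary outcome, the NEL, is self-rated by unblinded patients.

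**Working it through.** **Custody.** Side by side, Design and Allocation makes the central researcher a recipient of the result, while Recruitment makes the same person the operator of the list. A look-up that shows one result per entry would reconcile them, but neither section describes one.

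**Slots per cell** (number of blocks × block size; stated maximum 14):

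- Cell A: 2×4 + 2×2 = 12
- Cell B: 1×4 + 5×2 = 14
- Cell C: 0×4 + 7×2 = 14

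The stated 14 is reproduced for B and C. Cell A is 2 short.

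**Share in blocks of 2**, with weights 1:2:2, that is 0.2, 0.4 and 0.4:

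- Average over teams: 0.2×4/12 + 0.4×10/14 + 0.4×1 = 0.067 + 0.286 + 0.400 = 0.752.
- Pooled over slots: (4 + 20 + 28)/(12 + 28 + 28) = 52/68 = 0.765.

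**Predictability.** Assumptions: 1:1 within blocks; random block order within a cell; a guesser who knows the team's past allocations but not the drawn cell, names the arm that is behind, and tosses a coin when the arms are level.

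*Second patient.* The first block is a 4 with probability 0.2×2/4 + 0.4×1/6 = 0.1667. Within a block of 4 the first two allocations agree with probability 1/3. So patient 2 gets the opposite arm to patient 1 with probability 1 − 0.1667/3 = 94.4%.

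*Even-numbered patients among the first 10.* The guess fails only at the second place of a block of 4 whose first two allocations agree (probability 1/3).

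- Expected number of such second places among patients 1–10: 0.2×2 + 0.4×5/6 = 0.733.
- Expected errors in 5 guesses: 0.733/3 = 0.244.
- Correct: (5 − 0.244)/5 = 95.1%.

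*Odd-numbered patients among the first 10.* The guess beats a coin only at the third place of a block of 4 whose first two allocations agree.

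- Expected number of such third places: 0.2×1.5 + 0.4×4/6 = 0.567.
- Gain: 0.567 × 1/3 × 1/2 = 0.094.
- Correct: (2.5 + 0.094)/5 = 51.9%.

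*All of the first 10.* (4.756 + 2.594)/10 = **73.5%**, against 50% if unpredictable. Enumerating every sequence the scheme allows gives the same 73.5% (73.8% over 12 patients). It also shows that no better rule exists for this guesser, and that about 52% of allocations can be called with at least 90% certainty.

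**Strict certainty.** Without knowledge of the drawn cell, 3.8% of the first 10 allocations are certain (5.5% of the first 12). With the block structure known, half the slots in blocks of 2 are certain. In a block of 4, 1 + 1/3 of the 4 slots are certain, which is one third. Over whole lists this gives 0.752×0.5 + 0.248/3 = 0.459, or about 45%.

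**What larger blocks would achieve.** In simulation with blocks of 4 and 6, equally likely and in random order, the same rule is right for 67–68% of patients in teams of 6 to 14.

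**The case against.** *The list was exposed.* A reader might infer that the central researcher saw the sequence. The documents do not show that. Entering three items into a computerised list fits a look-up that returns one result, and emailing the condition to the central researcher would be needless if that person could read the list. The figure on the randomisation procedure is also not available here. What stands is an unreconciled contradiction.

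*Every second allocation was certain.* A reader might infer this for the teams on seven blocks of 2, or take the 45% as what staff knew. Both need knowledge of the block structure drawn for that team, which the protocol withholds. The 73.5% and 95% do not need it.

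*Patients beyond the list had no concealed allocation.* The summary of changes reports that "there was one team that included 18 patients", which is 4 more than 14. That is a report of conduct, and nothing says the statistician did not extend the list. It only shows that the handling needs documenting.

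*The short cell is trivial.* Largely true. It may be a slip for 2x4 and 3x2, and read literally it matters only when a team on that cell reaches patient 13. The expected mean was 10 per team. The actual mean was 158/(18 − 1 + 3) = 7.9.

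*Safeguards and trade-offs exist.* All incoming patients are to be checked and eligible ones informed, which limits selective invitation without removing it. Small blocks also serve the stated aim of limiting imbalance in small teams. Larger blocks leave about three quarters of the excess over 50%: roughly 17–18 of 23–24 percentage points. They improve predictability but do not cure it.

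**Conclusion.** The point holds in three parts of unequal weight.

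1. The protocol contradicts itself on who holds and operates the list. As written, its concealment claim is not supported, but it is not disproved either.
2. The stated unpredictability to care-givers is not delivered. Recruiting staff who remember their team's earlier allocations can guess 73.5% of the first 10 correctly, and about 95% of the even-numbered ones, without seeing the list or knowing the drawn cell. This rests on the stated cells and ratio, 1:1 allocation within blocks, random block order, and the staff who are sent the allocations being, or sharing information with, those who recruit.
3. The first cell holds 12 slots against a stated 14. It is a plain error with a small effect at about 10 patients per team.

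None of this shows that anyone used a guess or that selection bias occurred. It shows that the design did not exclude it to the extent claimed.

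**What to change.** **Text.** State in both sections that the independent statistician is sole custodian and releases one allocation per logged request, with the central researcher only forwarding requests. If a locked look-up was used, describe it instead. Correct the first cell so that it reaches 14 (for example 2x4 and 3x2), or state that 12 was intended. Say how a list is extended beyond its last slot. This costs wording only.

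**Scheme, for any further use.** Replace blocks of 2 with larger mixed blocks, for example 4 and 6, with sizes not disclosed to sites. The guess rate falls from 73–74% to about 67–68%. The share that is certain when the blocks are known falls from about 45% to 22–25%. The price is slightly more imbalance within a team: an open block of 6 can leave a difference of 3, against 1 or 2 for blocks of 2 or 4.

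**This trial.** Enrolment is complete, so the list cannot be regenerated. Withdraw or qualify the unpredictability claim and report the block scheme with its guess rate. Document who held the list and how any allocation beyond it was made. Add a sensitivity check: derive each patient's predicted arm from the team's earlier allocations (ahead, behind or level), compare baseline characteristics across predicted arms, and examine the primary NEL result by predicted arm. This needs only entry order, team and allocation. With 158 patients it can reveal gross selection but cannot rule out a modest amount.
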